### Other Study Measures

PACS assessed a number of safety measures and predictors of caries increment at baseline.

#### Medical History

At V1, V5, and V6, participants completed a medical history questionnaire indicating whether they had ever been diagnosed or treated for a series of common medical conditions. An additional medical-eligibility questionnaire was asked at the screening visit.

#### Oral Health History

At V1 and V6, participants completed a brief questionnaire regarding their oral hygiene practices and dental history.

#### Soft Tissue Examination

Participants were examined for abnormalities of the oral mucosa at V1, V5, and V6. An assessment for candidiasis was part of this examination. This assessment also provides additional data to the microbiology substudy at the Tufts clinical center.

#### Adverse Events

Starting at V1, participants were asked if they had experienced any adverse events since the last visit. Additionally, at the treatment visits they were asked if they had experienced any adverse events during the treatment application. All serious adverse events (SAEs) were immediately reported to the data-coordinating center, the Project Office, the Study Chair and CHX Technologies Inc.; CHX Technologies Inc., in turn, notified the FDA. The respective Institutional Review Boards of each institution were also notified of adverse events.

#### Medication Use

Prescription medication use was tracked at each clinic visit.

#### Demographic Information

Demographic information was collected as part of the screening visit.

#### Pregnancy Status

Pregnant women and women who were planning to conceive during the course of the study were excluded from participation. As a safety precaution, we confirmed pregnancy status again at V5 and pregnant women did not receive the final treatment application.

#### Acidic Drink Consumption

The consumption of acidic beverages can prematurely erode the protective coating that was applied in stage 2 of the treatment application process. Participants were asked to avoid drinking such beverages for three days following treatment application, and we asked about typical consumption of acidic beverages at the SV, V4, V5, and V6 visits.

#### Intervention and Dental Care Costs

Program cost and cost-effectiveness analyses of the chlorhexidine coating will be assessed from patient and dental plan perspectives [30]. Study staff conducted comprehensive chart reviews to document all dental-care procedures (CDT and local codes), procedure dates, billed claims, amount paid by insurance, and insurance plan type for encounters of study participants from the randomization date to V6. Procedures and clinical service costs related to SAEs were noted. We obtained clinical staff earnings and clinic facility space to estimate provider training and service delivery costs. We also included participant travel time and costs for each clinical visit. These data will be used to calculate the incremental net cost-effectiveness per prevented caries increment of the intervention, compared to placebo, for total and restoration-related dental care expenditures. All costs will be expressed in a reference year values (e.g., 2009 dollars). Expenditures and outcomes occurring in month 13 will be discounted to present value terms using a financial discount rate for the medical-care service sector. Sensitivity analyses will be conducted by varying key model inputs, and sub-group analyses will be conducted if supported by the data. We also conducted a price opinion survey at SV to estimate patients' willingness to pay for the service and to support a cost-benefit analysis of the intervention [31]. TCRHCC participants receive free out-of-pocket care and were excluded from the price survey.

### Quality Control

In addition to being trained as caries examiners and recorders, staff were centrally trained and certified in all aspects of study operations, including questionnaire administration, data entry, and application of the dental coatings. Initial training occurred prior to the start of randomization, with recertification occurring roughly annually. The data-coordinating center monitored study progress on an ongoing basis and generated regular trial monitoring reports for review by the Steering Committee and the Data Safety Monitoring Board (DSMB).

The data-coordinating center used a secure, web-based application for data entry and management. This application incorporated real-time error checking and quality assurance at the time of data entry and prompted clinical center staff about potentially erroneous data during data entry. Additional "back-end" checks were performed at the data-coordinating center.

In addition to the routine trial monitoring reports generated by the data-coordinating center, Internet-enabled reporting tools allowed authorized clinical center staff to access additional reports and edit data on an ad hoc basis. The data-coordinating center maintained an electronic audit trail of all errors and error resolutions.

PACS employed three types of site visit monitoring. CHX Technologies Inc. conducted their own ongoing monitoring. Schiff & Associates, an outside contractor employed by CHX Technologies Inc., conducted three independent monitoring visits at each clinical center--at the beginning, middle, and end of the study. And finally, the data-coordinating center conducted annual site visits at each clinical center to review all aspects of quality assurance, as defined in GCP [32].

### Data Analysis

Analyses will be carried out in three samples. The **intent-to-treat (ITT) **sample includes all randomized participants, regardless of their adherence to the protocol, and classifies them according to their assigned treatment group. The **per-protocol **sample consists of participants who received all five applications of their assigned study treatment, or who were removed from treatment due to an adverse event, and did not deviate from the protocol in any significant way that could have affected the results. The **safety **sample consists of all participants who received at least one study treatment. These individuals are classified according to the actual treatment received.

In order to include all randomized participants in the ITT sample, we will use multiple imputation [33] to impute missing caries examination data for the V6 (final) visit. The planned primary- outcome analysis will be repeated in exactly the same way in each of the imputed datasets, and the results combined using Rubin's [34] rules to produce the adjusted estimates and statistics from which inferences will be drawn.

All statistical hypothesis tests will be performed with two-sided type I error level of α=0.05. Interaction terms, when included in the model (e.g., treatment-by-site), will be assessed at α=0.10. No adjustment for multiple testing is planned.

#### Primary Analysis

The primary efficacy analysis will be in the ITT population, using analysis of covariance (ANCOVA), with treatment group, clinical center, and examiner included as categorical factors, and age and age-squared as continuous covariates. We will use rank-normalized net caries increment scores in this analysis. We next will evaluate whether an interaction exists between clinical center and treatment and, if so, will estimate and test center-specific treatment effects.

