Study Center	Recr quota	Fluoride in water	Dental reimbursement	Est. caries prevalence versus US average
KP Portland	400	Partly	Pre-paid managed care	Same

Tufts	200	Yes	Majority uninsured	Same

Dental Service of MA, Southborough	200	Partly	Primarily prepaid fee-for-service	Same

Tuba City	200	Partly	Access to free care	Higher

All participants attended an initial screening visit to assess eligibility. Eligible participants then received necessary restorative care for all cavitated lesions prior to returning for a randomization visit, at which time additional baseline measurements (including a baseline caries examination) were obtained. Individuals who still had cavitated lesions at this point were referred back to their treating dentist for further restorative care prior to randomization, and the randomization visit was then repeated.

Eligible participants were randomized to receive five applications of either a chlorhexidine (10% w/v) or placebo dental coating over a seven-month interval. A computerized randomization process confirmed participant eligibility prior to issuing randomization assignments. The latter were stratified by clinical center and age and, within each strata, clustered in blocks of varying sizes. Participants and staff were blinded to treatment assignment. Overall, we randomized 983 participants, close to our goal of 1000.

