#### Secondary Analyses

##### Secondary Aim 1

We will test whether the effect of the study medication differs within subgroups of the ITT sample defined by: baseline decayed filled surfaces (DFS) (median split), age (quartile groups), sex, and whether these added covariates account for any clinical center differences observed in the primary analysis.

##### Secondary Aim 2

We will evaluate incidence and increment of root and coronal caries in ITT participants by age, socioeconomic status (education, income), dental care setting (managed care, fee-for-service, etc.), and health-related profile.

##### Secondary Aim 3

We will evaluate the impact that various models of caries increment and detection criteria have on incidence and prevalence estimates of this most common adult disease.

##### Secondary Aim 4

We will evaluate the effect of the chlorhexidine (10% w/v) dental coating on resistant (*S. mutans*) and opportunistic (*C. albicans*) infections in the oral cavity using the subset of Tufts participants who are enrolled in the substudy.

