### Study Power

The power analysis takes account of the fact that we plan to transform the observed caries- increment scores to a normal distribution. We used a data simulation to determine what the impact of the transformation would be on the target effect size of 20% reduction in net caries increment. The results of our sample-size modeling, for varying effect sizes (Cohen's *d*, i.e., the ratio of mean difference to standard deviation (SD)), are shown in Figure 1. The 20% target effect size--expressed in rank-transformed units--is a *d *of 0.225, at which 416 randomized per group yields a power of 90%. The final target sample size of 1000 (500 per group) was deemed sufficient to provide adequate power, given what we believe to be conservative estimates of the effect size. These calculations do not adjust for attrition since we plan to use multiple imputation to obtain plausible replacement values for missing outcome measures.

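### The primary ANCOVA has no baseline caries covariate, although the V1 surface examination is held for everyone; this may cost precision but causes no bias

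*Protocol article*

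**What the plan says.** The Primary Analysis section sets the model terms: an ANCOVA in the ITT population "with treatment group, clinical center, and examiner included as categorical factors, and age and age-squared as continuous covariates", with rank-normalised net increment as the response. The article fixes this list itself, so the point is not a detail left to a separate analysis plan.

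A baseline caries examination is made at the randomisation visit (Study Population), and Table 3 shows the tooth surface examination at V1. The Primary Study Outcome section defines the net increment as the sum of surface transition scores from V1 to V6, and says that the bolded weights in Table 6 will be ignored in the primary analysis.

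A baseline caries measure enters the described analyses only in Secondary Aim 1, which lists "baseline decayed filled surfaces (DFS) (median split") among its subgroup factors. The same sentence also uses these factors as added covariates, to see whether they explain center differences. Randomisation is stratified by clinical center and age, not by caries status.

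**The concern.** The outcome is a change score, and what each surface can score depends on its V1 state. Participants differ in how many non-cavitated, sound, filled and unscorable surfaces they bring to V1, since entry requires only 20 intact teeth and unexposed roots are not scored. Baseline lesions may also mark a person's underlying caries risk. If either link is material, the variation that baseline status could explain stays in the residual of the primary model, and the treatment estimate is less precise than the collected data allow. The model also makes no adjustment if the arms happen to differ in baseline lesions.

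**Working it through.** **1. Score range by V1 state** (Table 6, bolded weights set to zero)

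| V1 state | Lowest | Highest |
|---|---|---|
| S, F, C | 0 | +2 |
| D1, FD1, CD1 | -1 | +1 |
| D2/D3 | 0 | +1 |
| FD2/FD3, CD2/CD3, Y, M | 0 | 0 |

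The only negative weights left are D1 to S, FD1 to F, CD1 to F and CD1 to C. A participant's lowest possible score is therefore minus the V1 count of D1 + FD1 + CD1 surfaces. Cavitated lesions are restored before randomisation, so non-cavitated lesions should be the main active lesions at V1.

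**2. The plan's own sample size**

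Inputs from Data Analysis and Study Power: "All statistical hypothesis tests will be performed with two-sided type I error level of α=0.05"; an effect size d "of 0.225, at which 416 randomized per group yields a power of 90" per cent; equal groups.

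n per group = 2(1.960 + 1.282)² / 0.225² = 2 × 10.507 / 0.050625 = 415.1, rounded up to 416. The stated figure reproduces.

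**3. Power at the size achieved**

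The Study Population section reports: "Overall, we randomized 983 participants, close to our goal of 1000". Taking 491 per group:

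power = Φ(0.225 × √(491/2) - 1.960) = Φ(3.525 - 1.960) = Φ(1.565) = 94.1%.

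This treats all 983 as carrying full outcome information, as the plan does ("These calculations do not adjust for attrition since we plan to use multiple imputation").

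**4. Effect of a baseline covariate**

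Let R² be the share of residual variance explained by V1 caries measures beyond center, examiner, age and age-squared. The residual SD becomes √(1 - R²), so 3.525 in step 3 is divided by √(1 - R²). The article gives no value for R²; the range below is assumed and starts at zero.

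| R² | Effective n multiplier, 1/(1 - R²) | CI width factor, √(1 - R²) | Power, 416 per group | Power, 983 randomised |
|---|---|---|---|---|
| 0 | 1.00 | 1.000 | 90.1% | 94.1% |
| 0.01 | 1.01 | 0.995 | 90.3% | 94.3% |
| 0.10 | 1.11 | 0.949 | 92.7% | 96.0% |
| 0.20 | 1.25 | 0.894 | 95.2% | 97.6% |
| 0.30 | 1.43 | 0.837 | 97.2% | 98.8% |

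The gain is larger if the true effect is below target. At an illustrative d = 0.18 with 983 randomised, power is 80.5% at R² = 0, and 84.4, 88.3 and 92.1% at R² = 0.10, 0.20 and 0.30.

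**5. Why one lesion count may not be enough**

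More D1-type surfaces mean more chances to score -1, but they may also mark higher risk of new lesions. A small simulation with assumed rates (983 people; mean D1 count 2, 5 or 10; reversal probability 0.1, 0.3 or 0.5; mean of 6 upward changes) gave correlations between baseline D1 count and rank-normalised increment from about -0.6 to +0.75. At mean count 5 and reversal probability 0.5, the correlation was -0.42 with no shared risk, -0.04 with half-shared risk and +0.47 with fully shared risk. The two effects can cancel, so DFS and the non-cavitated count should be separate terms.

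**The case against.** The strongest case is that this is an optional efficiency gain in a valid model. Power is already about 94% at the design effect. Center, examiner and a quadratic in age are in the model and may absorb part of the baseline differences. The correlation is unknown, and near zero there is nothing to gain. All of this stands and sets the size of the point.

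Four stronger readings are tempting, but the article does not support them.

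- *The bounds in Table 6 prove that precision is lost.* A bound is not a correlation. With 20 or more teeth and several surfaces on each, the upper limit is very unlikely to bind. The workable links are the floor set by non-cavitated lesions and shared caries risk, and the article quantifies neither.
- *A chance imbalance in D1 lesions passes straight into the result.* Only lesions that revert score -1; others progress and score +1, and the total is then rank-normalised. Even the direction is unknown, and the two-sided test already allows for chance imbalance.
- *Baseline DFS serves only as a subgroup factor.* Secondary Aim 1 also uses it as an added covariate, though not in the primary test.
- *The mention of "predictors of caries increment at baseline" under Other Study Measures shows that the plan itself regards baseline caries as a predictor.* That heading introduces questionnaires, the soft tissue examination, safety items and costs, not the caries examination.

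What remains is that the outcome's own baseline examination is held for everyone, is a plausible predictor, and is left out of the primary model.

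**Conclusion.** The point holds as a possible loss of precision and a missing adjustment for chance imbalance in baseline lesions. It is a free improvement, not an error. A reader might infer that the primary comparison is biased or the trial underpowered; neither follows. Treatment is randomised, 416 per group reproduces, and the number randomised exceeds 2 × 416 = 832.

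The size is uncertain. With 983 randomised and d = 0.225, power moves from 94.1% to between 94.1% (R² = 0) and 98.8% (R² = 0.30), and the confidence interval narrows by between nothing and about 16%. This rests on an assumed R², on d = 0.225 being expressed against the residual SD of the present model, and on no loss of information from missing V6 examinations. The V1 facts and score ranges are certain; the magnitude is not.

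**What to change.** Before unblinding, amend the primary ANCOVA to add, as continuous V1 covariates in separate terms:

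- baseline DFS;
- the number of non-cavitated lesion surfaces (D1 + FD1 + CD1);
- optionally, the number of scorable surfaces.

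State the functional form of each in advance, and make sure the imputation model contains the same variables. The article does not list that model's variables, so this is a consistency requirement and not a reported gap.

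The cost is two or three degrees of freedom out of 983 participants and no new data. It does change the primary model of a pivotal study under an IND after recruitment has closed, so it needs a dated, documented amendment. If unblinding has already taken place, keep the stated model as primary and report the adjusted model as supportive.

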#### Secondary Analyses

##### Secondary Aim 1

We will test whether the effect of the study medication differs within subgroups of the ITT sample defined by: baseline decayed filled surfaces (DFS) (median split), age (quartile groups), sex, and whether these added covariates account for any clinical center differences observed in the primary analysis.

##### Secondary Aim 2

We will evaluate incidence and increment of root and coronal caries in ITT participants by age, socioeconomic status (education, income), dental care setting (managed care, fee-for-service, etc.), and health-related profile.

##### Secondary Aim 3

We will evaluate the impact that various models of caries increment and detection criteria have on incidence and prevalence estimates of this most common adult disease.

##### Secondary Aim 4

We will evaluate the effect of the chlorhexidine (10% w/v) dental coating on resistant (*S. mutans*) and opportunistic (*C. albicans*) infections in the oral cavity using the subset of Tufts participants who are enrolled in the substudy.

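### Testing effect modification on a DFS median split and age quartile groups gives up power if the modification is roughly monotone; continuous interaction terms would recover it at little cost

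*Protocol article*

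**What the plan says.** In the protocol article, Secondary Analyses, Secondary Aim 1 opens: "We will test whether the effect of the study medication differs within subgroups of the ITT sample defined by". It then lists the groupings: "baseline decayed filled surfaces (DFS) (median split), age (quartile groups), sex". The same sentence asks whether these covariates account for any clinical center differences seen in the primary analysis. It does not say in which form DFS enters that second step.

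The Data Analysis section sets the test level: "Interaction terms, when included in the model (e.g., treatment-by-site), will be assessed at α=0.10". It adds: "No adjustment for multiple testing is planned".

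The Primary Analysis section carries "age and age-squared as continuous covariates" in the ANCOVA, with rank-normalized net caries increment as the outcome.

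No continuous treatment-by-DFS or treatment-by-age interaction is described anywhere in the article. The Study Power section gives power for the main effect only.

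**The concern.** Baseline DFS is a count with many values, and age is recorded in years. Cutting DFS at its median treats everyone on one side of the cut as alike. Cutting age into four groups does the same within each quartile and, if the groups are unordered, spends three degrees of freedom. When the effect rises or falls steadily with the modifier, both steps discard part of the signal that the aim is looking for.

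Interaction tests are weak in a trial sized for its main effect, and recruitment has closed at 983. The form of the model is therefore one of the few ways left to gain information for this aim. At stake is a missed interaction in a secondary analysis, not the primary conclusion.

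**Working it through.** **Inputs from the article.** Randomized N = 983; interaction alpha 0.10; d = 0.225 and 416 per group for 90% power (Study Power); rank-normalized outcome, SD taken as 1.

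**Assumed, because the article does not give them.** 1:1 allocation, the distribution of the modifier, a linear interaction, and a starting power of 80% for the continuous 1-df test.

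**1. The plan's own figure.** n per group = 2 × [(1.960 + 1.282) / 0.225]² ≈ 415.1, rounded up to 416; power at 416 is 0.901. The stated figure reproduces. There is no stated interaction power to reproduce.

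**2. Reference interaction.** The test statistic is noncentral chi-square with λ = slope² × N/4, where the slope is the change in treatment effect (in outcome SDs) per SD of the modifier. For 80% power at alpha 0.10 on 1 df, λ = 6.182. The slope is √(6.182 / 245.75) = 0.159.

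**3. Share of a linear signal kept by grouping.** This is the between-group variance of the modifier divided by its total variance, and λ shrinks by that share. For a normal modifier the median split keeps 2/π = 0.637, so λ = 6.182 × 0.637 = 3.94. Power is then 63%. At alpha 0.05, starting again from 80%, it is 61%.

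**4. Other distributions** (continuous linear test at 80%, alpha 0.10):

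| Modifier | Kept, median split | Power, median split | Kept, quartiles | Power, quartiles (3 df) |
|---|---|---|---|---|
| Uniform | 75% | 69% | 94% | 63% |
| Normal | 64% | 63% | 86% | 59% |
| Gamma, shape 2 | 55% | 58% | 79% | 56% |
| Lognormal, sigma 0.7 | 42% | 49% | 65% | 49% |

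The skewed rows assume that modification is linear in the raw value. If it is linear in the log of a lognormal modifier, the normal row applies; if linear in the rank, the uniform row applies.

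**5. Age: the result depends on the form of test** (normal modifier, same λ = 6.182):

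| Test of treatment × age | df | Power |
|---|---|---|
| Linear | 1 | 80% |
| Quartiles scored as a trend (keeps 86%) | 1 | 74% |
| Age plus age-squared | 2 | 71% |
| Unordered quartiles | 3 | 59% |

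Starting from 90% instead, the median split gives 76%, quartile trend 86%, age plus age-squared 84% and unordered quartiles 73%.

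**6. Shapes other than linear** (normal modifier). If the effect steps exactly at the median, the split keeps the whole signal and a linear term keeps 64%, so the ranking reverses. If modification is purely quadratic, a linear term keeps nothing, quartiles keep about 37%, and age plus age-squared keeps all of it.

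**The case against.** The strongest reply is that nothing here is wrong. The groups are fixed in advance, the aim is secondary, and subgroup results are easy to read. This largely stands: the point is an improvement in efficiency, not an error. It remains a fair comment because the article itself names the groupings and describes no continuous test.

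Several stronger readings are tempting, and the documents do not support them:

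- **That a cut at the sample median biases the test.** The median of a baseline covariate is chosen without sight of outcome or treatment effect, so it does not inflate type I error.
- **That quartiles turn a 1-df test into a 3-df test.** The continuous form matching the primary model has 2 df. The gap is about 71% against 59%, not 80% against 59%, and it disappears if the quartiles are scored as a trend (74%).
- **That continuous age for adjustment contradicts grouped age for subgroups.** The two uses serve different purposes.
- **That the cut-offs do not carry to other populations.** The aim concerns subgroups of this trial's ITT sample and proposes no clinical threshold.
- **That center differences will be left confounded by DFS.** Secondary Aim 1 does not say whether DFS enters that model split or continuous. For age, the primary model already carries continuous terms.

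It is also fair to say that continuous terms will not make the aim decisive. The reference slope of 0.159 is about 70% of the planned main effect (0.159 / 0.225). At half that slope λ falls to a quarter, 1.546, and power is about 35% continuous against 26% with the median split. The relaxed alpha of 0.10 does not answer the point, since it applies equally to grouped and continuous tests.

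**Conclusion.** The point holds as a low-severity suggestion. If modification is roughly monotone, grouping costs power. For DFS, 80% becomes about 63% with a normal modifier, and 49% to 69% across the other distributions tried. For age, unordered quartiles give about 59% against about 71% for the form already in the primary model; a quartile trend would remove that gap. These figures rest on a linear interaction, an assumed distribution and a hypothetical 80% starting point, none of which the article supplies. With a true step at the median, the planned split is the better test. A reader might infer that Secondary Aim 1 is invalid or that the primary result is at risk. Neither follows: the planned tests keep their error rate, and the primary analysis, its alpha and its sample size are untouched.

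**What to change.** In Secondary Aim 1, make the interaction tests treatment × continuous DFS (log- or rank-scaled, in view of likely skew) and treatment × age with age-squared, both within the ANCOVA at the interaction level already set. State that DFS enters as a continuous term when asking whether covariates account for center differences. Keep the median and quartile groups for displaying effects.

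The change is to wording only and needs no new data. The cost is an assumption about functional form. Adding a quadratic DFS term checks it for DFS; age already has one.
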